### 1.4. Correlation with Menstrual Parameters, Serum, and Ultrasound

While there have been unpublished data demonstrating internal validity by the Mira monitor manufacturers, there have not been any formal studies comparing it to the gold standard of the estimated day of ovulation on ultrasound, and serum correlations need to be externally validated. These results should also be contextualized with regard to ovarian reserve with serum anti-Müllerian hormone (AMH) levels [36]. Besides hormonal variations, other key parameters of the menstrual cycle include bleeding patterns and vital sign changes. Bleeding patterns during menses and throughout the cycle are a barometer of menstrual health, and there are multiple bleeding scores to monitor these changes [37], but it is important to use a score that has been validated against a physical measurement of fluid loss like the Mansfield–Voda–Jorgensen Menstrual Bleeding Scale [38].

In addition, temperature changes in the menstrual cycle (i.e., the temperature shift after ovulation, see Figure 1E) have been known for many years and have been used to guide fertility assessment [39,40]. It should be emphasized that these menstrual cycle biomarkers require correlation with the gold standard of serum hormonal measurements and serial endovaginal ultrasound to track follicular development and ovulation. Previous studies have shown that the ultrasound-based day of ovulation is highly correlated with urinary hormones [41,42,43,44]. Our primary objective in this protocol will be to establish this correlation specifically for the Mira monitor.

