## 2. Materials and Methods

### 2.1. Objective and Hypothesis

Our objective is to characterize quantitative hormones in the urine using the Mira monitor and validate these in reference to serum hormonal measurements and the gold standard of the ultrasound day of ovulation in participants with normal (regular) menstrual cycles. This will also help to establish external validity for the Mira monitor for use in women with regular cycles, rather than relying on industry-based internal data. We will then compare those with regular cycles to oligomenorrheic women with polycystic ovarian syndrome (PCOS) and oligomenorrheic athletes.

We hypothesize that the Mira monitor’s detected urine hormone pattern will accurately correlate with serum hormonal levels and will predict (LH) and confirm (PDG) the ultrasound day of ovulation in those with regular cycles as well as those with oligomenorrheic cycles.

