### 2.4. Recruitment and Sample Size Considerations

Recruitment will occur through the University of Calgary social media and research sites. We anticipate that a snowball sampling effect will also occur. Interested participants will be contacted by a research assistant to complete an online survey to ensure they meet the inclusion criteria (Table 1 and Table 2).

Previous ultrasound studies validating urine hormone monitor measurements have targeted 50 participants over 3 cycles, for a total of 150 menstrual cycles [41]. With 150 cycles for analysis, the study would be adequately powered to detect differences of 0.5 days in the estimated day of ovulation, cycle length, and follicular/luteal phase lengths. This calculation was done with G*Power 3.1, with an effect size of 0.2, alpha 0.05, and power of 80%. This calculation is valid for correlation statistics with an a priori power analysis with one tail. Oversampling up to 60 participants may be required to ensure that we have 150 cycles for analysis. The same sample size will be used for recruitment of the PCOS and athlete groups. We know that the participant burden is high, and therefore, we are prepared to continue to recruit until we reach sample size.

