## 3. Results (Planned)

### 3.1. Data Analysis

Datasets will be analyzed using SPSS version 29 (IBM, Chicago, IL, USA) and charts prepared using SPSS or Excel (Microsoft, Redmond, WA, USA). Descriptive statistics will be used to determine the means, standard deviations (SD), and 95% confidence intervals (CI) of the menstrual cycle parameters, i.e., cycle length, day of ovulation, length of the follicular phase and the luteal phase, menstrual bleeding scores, and duration. The ultrasound-defined day of ovulation (US-DO) will be considered day 0 as a reference for days leading up to and after ovulation. The main analysis in this sample (for which it is powered) will be to correlate (with Spearman’s correlation coefficients) the day of ovulation with peak levels of LH on the Mira monitor, as well as with the day of progesterone elevation, to confirm ovulation. Sensitivity and specificity analyses of each hormone in relation to the US-DO will be calculated.

Secondary exploratory data analyses (not considered in the power calculations) will include daily average hormone values from the Mira monitor referenced to day 0 (US-DO), average hormone values, 95% confidence individuals on days leading up to ovulation (days −5, −4, −3, −2, −1, etc.), and after ovulation (days +1, +2, +3, +4, +5 etc.) from cycle day 6 until the end of the cycle. Daily means, SDs, and CIs of hormone values across the study sample will be used to describe the variability in the population, as was done in the pilot study [34], and individual (personalized) hormone patterns will also be considered as we have presented in previous studies [51]. Day-to-day hormone variability will require complex modelling of hormonal patterns, which we have used in previous studies [53], using *R*-software (*R* Foundation for Statistical Computing, Vienna, Austria). The specific statistical methods involve creating best-fit distributions for wave patterns of the hormones using the mean square of residuals as the loss function, with the goal to minimize the loss function to improve the fit of the distribution based on the density of the hormone wave patterns in the population; this specific method has helped to identify distinct hormone patterns that may represent different physiologic mechanisms, but it must be emphasized that these are hypothesis-generating rather than primary endpoints of this proposal.

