### 3.3. Anticipated Results

We expect that the Mira monitor will accurately and precisely identify and confirm the day of ovulation as shown on ultrasound. Bleeding patterns and menstrual cycle observations will provide a baseline pattern for normal healthy participants to compare to abnormal cycles. We may be able to further expand on previous work related to daily quantitative hormone patterns, for example, by modelling estrogen changes from follicular wave activity in the early follicular phase [56], demonstrating the diversity of LH profiles related to ovulation patterns [57], or showing luteal progesterone variability [52,58]. The results from this study will potentially provide nomograms for urinary hormone measurements and provide reference values for future studies evaluating menstrual health.

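### The main, powered analysis is a Spearman correlation, which does not measure agreement in days and so cannot by itself support the conclusion that the monitor accurately identifies the ultrasound day of ovulation

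*Protocol article*

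**What the plan says.** Section 3.1 of the protocol article introduces the analysis with "The main analysis in this sample (for which it is powered" and states that it "will be to correlate (with Spearman’s correlation coefficients) the day of ovulation with peak levels of LH on the Mira monitor". A second correlation, meant to confirm ovulation, uses the day on which progesterone rises. I read this as the day of the LH peak and the day of the urinary PDG rise. Taken literally, a peak level is a concentration, and correlating that with a day would say even less about timing.

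The conclusions to be drawn concern days. The hypothesis in section 2.1 is that the urine hormones "will predict (LH) and confirm (PDG) the ultrasound day of ovulation in those with regular cycles as well as those with oligomenorrheic cycles". Section 3.3 states: "We expect that the Mira monitor will accurately and precisely identify and confirm the day of ovulation as shown on ultrasound". Section 4.4 foresees that, once validated, the monitor can be relied on without ultrasound in every study. Section 1.4 words the aim more narrowly: "Our primary objective in this protocol will be to establish this correlation specifically for the Mira monitor".

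Section 2.4 sizes the study to match a correlation: "This calculation was done with G*Power 3.1, with an effect size of 0.2, alpha 0.05, and power of 80" per cent, one-tailed, for 150 cycles from 50 participants. The same section says that this gives power for differences of 0.5 days.

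Two other analyses in section 3.1 bear on timing. One is sensitivity and specificity of each hormone against US-DO, with no day window stated. The other is a set of daily mean hormone curves aligned to US-DO, labelled exploratory and outside the power calculation.

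**The concern.** A validation claim of this kind needs to know how many days separate the monitor's day from the ultrasound day in a given cycle, and how much that gap varies. Spearman's coefficient reports neither. It measures how well two sets of days keep the same rank order. Adding the same number of days to every monitor reading leaves the ranks, and therefore rho, unchanged. Because both events are counted from day 1 of the same cycle, rho also depends on how widely ovulation days are spread in the sample, which is a property of the participants and not of the monitor.

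The headline result could therefore be high and significant whether the monitor's timing is good or poor. In addition, a coefficient from the PCOS or athlete group could exceed that of the regular group simply because ovulation days vary more there.

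**Working it through.** **Inputs from the article.** Section 2.4 gives effect size 0.2, alpha 0.05 one-tailed, power 80%, 150 cycles, and 50 participants with 3 cycles each. The article gives no SD for ovulation day or monitor error, so every SD and offset below is an assumption, shown over a range. The result for a constant shift needs no SD.

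**1. The plan's own figure.** A point-biserial correlation test with rho = 0.2 and one-sided alpha 0.05 needs N = 150 for 80% power (power at 150 = 0.8006), so the stated figure is reproduced. The Fisher z formula gives ((1.645 + 0.842)/atanh 0.2)² + 3 = 153.4, which is close. At n = 150 the one-sided 5% critical correlation is about 0.135. Two events counted from the same cycle start will pass that very easily.

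**2. Constant shift.** Let U be US-DO and M = U + 3 in every cycle. The ranks of M equal those of U, so rho = 1.000, while no cycle is within 1 day. The same holds for 5 days or −3 days.

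**3. Offset plus random error.** Take U = round N(μ, sdU) and M = round(U + b + N(0, sdE)).
- Share within 1 day = Φ((1.5 − b)/sdE) − Φ((−1.5 − b)/sdE).
- As a guide to rho, the Pearson value without rounding is sdU/√(sdU² + sdE²), in which b does not appear.

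| sdU | offset b | sdE | Pearson guide | simulated Spearman rho | within ±1 day |
|---|---|---|---|---|---|
| 3 | 0 | 1 | 3/√10 = 0.95 | 0.94 | 87% |
| 3 | 3 | 1 | 3/√10 = 0.95 | 0.94 | 7% |
| 3 | 0 | 2 | 3/√13 = 0.83 | 0.82 | 55% |
| 10 | 0 | 2 | 10/√104 = 0.98 | 0.98 | 55% |
| 10 | 0 | 3 | 10/√109 = 0.96 | 0.95 | 38% |

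Rows 1 and 2 have the same rho but opposite timing performance. Rows 3 and 4 have the same performance but different rho. Row 5 has a larger error than row 3, yet a higher rho.

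**4. Varying error.** With no offset, sdE = 3 and sdU from 2 to 5, simulated rho at n = 150 is 0.53 to 0.84, with about 38% of cycles within 1 day. So rho does fall, but the test against zero was significant in every one of 300 runs per setting.

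**5. What 150 cycles give for a difference in days.** The 95% CI half-width of the mean difference is t × SD/√n.
- Independent cycles, n = 150: 1.976 × 1/√150 = 0.16 days for SD 1, and 1.976 × 3/√150 = 0.48 days for SD 3.
- Cycles within a woman fully correlated, effective n = 50: 2.01 × 1/√50 = 0.28 days for SD 1, and 2.01 × 3/√50 = 0.85 days for SD 3.
- Share within 1 day, Wilson 95% CI, independent cycles: 120/150 = 80% (72.9 to 85.6%); 135/150 = 90% (84.2 to 93.8%).

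The planned sample therefore supports an analysis in days.

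**The case against.** The strongest reply is that the analysis matches the objective as worded in section 1.4, which is to establish a correlation, and that section 3.3 states an expectation and not a success criterion. That explains the choice of statistic. It does not allow an accuracy conclusion to be drawn from it, and the hypothesis in section 2.1 is about the ultrasound day.

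A second reply is that other planned analyses would expose an offset. In part they would: the sensitivity and specificity analysis is not labelled exploratory, and curves aligned to US-DO would display an average shift. But no day window is stated for the former (the full protocol may hold it), and the curves are exploratory averages that do not give the error in individual cycles.

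A third reply is that LH should precede ovulation and PDG should follow it, as the legend of Figure 1 describes, so a stable lag is compatible with predicting and confirming. This stands. It means that a non-zero mean difference is not in itself a failure, and that the 0.5 days of section 2.4 cannot serve as a margin. That section gives it as a detectable difference in ovulation day, cycle length and phase lengths, not as monitor day minus US-DO. But rho reports neither the size of the lag nor its spread in days.

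Stronger readings are tempting and should not be made:
- A reader might infer that the correlation cannot be computed because US-DO "will be considered day 0 as a reference for days leading up to and after ovulation". That is an alignment convention. The same section lists day of ovulation among the parameters to be given a mean and SD, so it varies as a cycle day.
- A reader might infer that the plan will compare coefficients between groups. Section 2.1 announces a comparison but names no statistic.
- A reader might infer that any inaccurate monitor would score near 1. That needs a roughly constant offset, or an error small relative to the spread of ovulation days.

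**Conclusion.** The point holds in this form: the main analysis, as fixed in section 3.1, cannot support the conclusion stated in section 3.3, because it does not measure agreement in days. The result for a constant shift (rho = 1.000, 0% within 1 day at 3 days) rests on no assumption. The other figures rest on assumed SDs and whole-day rounding: rho 0.94 with either 87% or 7% of cycles within 1 day, and rho 0.82 or 0.98 with the same 55%. Coefficients from regular and irregular groups, if set side by side, would not be comparable as measures of accuracy. The documents do not show that the monitor is in fact offset, nor that an offset would go unseen. They show that the powered result does not report per-cycle error.

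**What to change.** Make the main analysis the per-cycle difference in cycle days: day of Mira LH peak minus US-DO, and day of PDG rise minus US-DO. Report, by group and by hormone, the mean lag, SD, 95% limits of agreement, and the proportion of cycles within ±1 and ±2 days of US-DO or of a prespecified expected lag, with confidence intervals clustered on participant. Do not use 0.5 days as a pass/fail margin. State that the LH quantity is the day of the peak and not its level. Keep Spearman as a secondary descriptive statistic.

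Restate the sample-size paragraph in section 2.4 as the precision of the mean difference, giving both the independent-cycle range and the worst-case clustered range derived above.

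The cost is rewording of the analysis and sample-size sections. No new data or participants are needed. The headline figure will look less favourable than a correlation.

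### The LH half of the powered main analysis is worded as ovulation day against an LH concentration, which cannot show whether the LH peak predicts the ultrasound day

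*Protocol article*

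**What the plan says.** Section 3.1 (Data Analysis) of the protocol article names one main analysis and says that the sample is powered for it: to "correlate (with Spearman’s correlation coefficients) the day of ovulation with peak levels of LH on the Mira monitor". The LH variable is therefore a level. For progesterone the wording is different, and the variable is a day: "as well as with the day of progesterone elevation, to confirm ovulation".

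The same section uses two scales for ovulation. It lists the day of ovulation among the "menstrual cycle parameters, i.e., cycle length, day of ovulation, length of the follicular phase and the luteal phase" to be summarised by mean, SD and confidence interval. It also says: "The ultrasound-defined day of ovulation (US-DO) will be considered day 0 as a reference for days leading up to and after ovulation". The second scale reappears in the exploratory analyses, which describe "daily average hormone values from the Mira monitor referenced to day 0 (US-DO").

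The aim is about timing throughout. Section 2.1 hypothesises that LH will predict, and PDG confirm, the ultrasound day. Section 2.4 expresses the detectable difference as 0.5 days. Section 3.3 states: "We expect that the Mira monitor will accurately and precisely identify and confirm the day of ovulation as shown on ultrasound".

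**The concern.** Correlating ovulation day with the height of the LH peak asks whether women who ovulate later have higher or lower peaks. The hypothesis asks something else: whether the peak falls at a predictable distance from ovulation. The article shows that it can name a timing variable, since it does so for progesterone in the same sentence, but it does not do so for LH.

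This coefficient carries the LH limb of the hypothesis in the only analysis that was sized. If the wording is followed, an accurate monitor could give a coefficient near zero and seem to fail. A non-zero coefficient could be reported as validation when it shows only a link between LH amplitude and follicular-phase length. If the wording is silently departed from, a reader cannot tell which of the two coefficients was prespecified. The same sample size is planned for the PCOS and athlete groups, so the ambiguity may carry over to them.

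**Working it through.** **1. The plan's own figure.** Section 2.4 says "This calculation was done with G*Power 3.1, with an effect size of 0.2, alpha 0.05, and power of 80" per cent, and adds: "This calculation is valid for correlation statistics with an a priori power analysis with one tail". Testing r = 0.2 against 0, one-sided alpha 0.05, power 0.80:

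- Noncentral t (point-biserial correlation model): the smallest n is 150, with power 0.8006.
- Fisher z: n = ((1.645 + 0.842) / atanh(0.2))² + 3 = (2.487 / 0.2027)² + 3 ≈ 153.4, rounded up to 154. Power at 150 is 0.792.

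The stated 150 cycles are reproduced, with cycles treated as independent. The figure fixes a correlation size, alpha and power, and says nothing about which LH variable enters. Changing the LH variable from a level to a day leaves it at 150.

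**2. What the literal coefficient depends on.** For cycle i, let D be the ultrasound day of ovulation, L the day of the highest LH reading, and H the height of that reading. As worded, the coefficient is Spearman(D, H). L does not appear in it. For given heights, any error or shift in L leaves the coefficient unchanged. This holds whatever the relation between H and D.

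**3. Three made-up cycles, checked by hand.** D = 13, 16, 20; L = 12, 15, 19 (always one day earlier); H = 65, 22, 41.

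- D against L: identical ranks, so rho = 1.0.
- D against H: ranks 1, 2, 3 against 3, 1, 2. Squared rank differences are 4 + 1 + 1 = 6. rho = 1 − 6 × 6 / (3 × (9 − 1)) = 1 − 36/24 = −0.5.

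Timing is perfectly consistent, yet the literal coefficient is negative.

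**4. Simulation.** The documents give no distribution for these variables, so all inputs are assumptions: 150 cycles per study, ovulation on cycle day 16 (SD 3), LH peak one day earlier plus a shift and a random error, peak height log-normal and unrelated to day; 500 simulated studies per row.

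| Shift in LH-peak day | Error SD (days) | Day vs level, mean rho | Day vs day, mean rho | Mean of L − D (days) |
|---|---|---|---|---|
| 0 | 1 | 0.00 | 0.94 | −1.0 |
| 0 | 4 | 0.00 | 0.58 | −1.0 |
| +3 | 1 | 0.00 | 0.94 | +2.0 |
| −3 | 1 | 0.00 | 0.94 | −4.0 |

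The day-against-level coefficient varies between studies with an SD of about 0.08 but does not respond to timing quality in any row. The day-against-day coefficient responds to random error but not to a 3-day shift, because adding a constant to every L leaves the ranks unchanged. Only the last column shows the shift.

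**5. The scale of the ovulation day.** A variable that is 0 in every cycle has no rank variance, and Spearman's coefficient is then undefined. That would apply only if the aligned scale entered the correlation. Section 3.1 gives the day of ovulation a mean and SD, so it varies there, and the section uses day 0 to align hormone values.

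**The case against.** The strongest reply is that this is a slip whose meaning is clear. The parallel phrase for progesterone, the hypothesis in Section 2.1, the 0.5-day figure in Section 2.4 and the expectation in Section 3.3 all point to the day of the LH peak. Section 1.4 uses similar shorthand when it speaks of correlating the ultrasound day with urinary hormones. Section 3.1 also plans sensitivity and specificity for each hormone against the ultrasound day, so the coefficient is not the only look at LH. All of this stands, and a slip is the likeliest explanation. It does not dispose of the point: the variable is stated rather than left to a fuller document, and what is stated does not measure the aim.

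Three stronger readings are tempting, and the documents do not support them.

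- A reader might infer that the main analysis cannot be computed because ovulation is set to day 0. The day-0 sentence limits itself to serving as a reference for surrounding days, and the same paragraph summarises the day of ovulation as a varying cycle parameter. It is fair to ask only that the scale be named.
- A reader might infer that the whole main analysis is mis-specified. The progesterone half pairs two days and is sound on the cycle-day scale.
- A reader might infer that power collapses from 80% to about 5%. Under an assumed independence of peak height and ovulation day, a 5% rejection rate is simply the type I error. The planned 80% refers to a true correlation of 0.2, so the two figures are not comparable.

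**Conclusion.** Wrong as written, for the LH half only. The literal coefficient does not contain the day of the LH peak, so it carries no information on whether that peak predicts the ultrasound day. This follows from the definition and needs no distributional assumption. The particular values in the simulation (about 0.00 against 0.94 or 0.58) rest on assumed distributions, above all on peak height being unrelated to ovulation day. If the two were related, the literal coefficient would differ from zero but would still not measure timing.

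The sample size of 150 cycles reproduces and does not change. As the plan is written, the coefficient is not undefined.

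**What to change.** In Section 3.1:

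1. Replace the reference to LH peak levels with the cycle day of the highest LH reading on the Mira monitor.
2. State that, in the main correlation, the ultrasound day, the LH-peak day and the day of progesterone elevation are all counted in cycle days from the first day of menses. Keep the scale with the ultrasound day as day 0 for the aligned hormone curves and for signed differences.
3. Report LH-peak day minus ultrasound day beside the correlation, as a mean with limits of agreement, because the rank correlation does not detect a constant shift.
4. If the relation between LH peak height and ovulation day is of interest, list it as exploratory.

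If a fuller protocol or analysis plan already defines the LH variable as a day, bring the article into line with it. The cost is a few sentences. Section 2.6 already has participants test first-morning urine daily for LH, so no extra data or participants are required.

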## Abstract

*Background and Objectives*: The Quantum Menstrual Health Monitoring Study will measure four key reproductive hormones in the urine (follicle-stimulating hormone, FSH; estrone-3-glucuronide, E_1_3G; luteinizing hormone, LH; and pregnanediol glucuronide, PDG) to characterize patterns that predict and confirm ovulation, referenced to serum hormones and the gold standard of the ultrasound day of ovulation in participants with regular cycles. These normal cycles will provide a reference for comparison to irregular cycles in subjects with polycystic ovarian syndrome (PCOS) and athletes. *Materials and Methods*: Participants will track their menstrual cycles for 3 months and be provided with an at-home urine hormone monitor (Mira monitor) to predict ovulation. The day of ovulation will be confirmed with serial ultrasounds completed in a community clinic. Urine results will be compared to serum hormone values. Other markers of menstrual health, such as bleeding patterns and temperature changes, will be determined using a customized app. Three groups will be recruited. Group 1 will include those with consistent regular cycle lengths (between 24–38 days), and will be compared to two groups with irregular cycle lengths (with increased cycle length variability and longer cycles). Group 2 will include those with polycystic ovarian syndrome (PCOS) with irregular cycles and Group 3 will include individuals participating in high levels of exercise with irregular cycles. *Hypothesis*: The Mira monitor quantitative urine hormone pattern will accurately correlate with serum hormonal levels and will predict (with LH) and confirm (with PDG) the ultrasound day of ovulation in those with regular cycles as well as those with irregular cycles. *Rationale*: Once the ultrasound validation is complete, tools like the Mira monitor with a customized app may become a new standard for at-home and remote clinical monitoring of the menstrual cycle without having to use labor-intensive follicular-tracking ultrasound or follow serum hormone changes. *Conclusions*: Precision monitoring of the menstrual cycle is expected to impact individuals who want to increase their menstrual health literacy and guide decisions about fertility.

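### The powered main analysis correlates ovulation day with a retrospectively identified LH peak, so by itself it tests association and not the stated hypothesis that LH predicts ovulation.

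*Protocol article*

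**What the plan says.** Section 2.1 gives the two urinary hormones separate roles: the monitor "will predict (LH) and confirm (PDG) the ultrasound day of ovulation in those with regular cycles", and the same sentence extends this to oligomenorrheic cycles. The Abstract repeats the hypothesis and describes the device as an "at-home urine hormone monitor (Mira monitor) to predict ovulation".

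Section 3.1 fixes the analysis: "The main analysis in this sample (for which it is powered) will be to correlate", by Spearman's coefficient, ovulation day "with peak levels of LH on the Mira monitor, as well as with the day of progesterone elevation, to confirm ovulation". Confirmation is the only purpose that sentence names. It mentions no LH surge onset, threshold or day-by-day rule.

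The next sentence adds: "Sensitivity and specificity analyses of each hormone in relation to the US-DO will be calculated". Daily hormone values on the days before ovulation appear only among the exploratory analyses, which section 3.1 places outside the power calculation.

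Section 1.4 states the primary objective as establishing, for this monitor, the correlation between urinary hormones and the ultrasound day that earlier studies found. Section 2.6 sets one first-morning urine test per day.

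**The concern.** Prediction means that on a given morning, with the values available so far, the monitor signals that ovulation is coming. The cycle maximum of LH does not have that property, because the analyst needs later values to know which day was the maximum. A rank correlation adds a second gap: it asks whether women with later peaks ovulate later, not whether the peak comes first or by how much.

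The wording adds an ambiguity. The LH half of the sentence names levels and the progesterone half names a day. Taken literally, the LH half relates ovulation timing to LH concentration.

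At stake is what the headline result may be used to claim. Section 4.2 foresees use of the monitor in planning conception, and section 4.4 foresees later studies relying on it without ultrasound. A high retrospective rho could be reported as proof of prediction when real-time performance had not been measured.

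**Working it through.** **1. The plan's own figure.** Section 2.4 gives effect size 0.2, one-tailed alpha 0.05, 80% power, a correlation test and 150 cycles.

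- Test of a correlation against zero with the noncentral t (point-biserial model): noncentrality = 0.2/√(1 − 0.04) × √N. At N = 150 this is 2.50 and power is 80.1%. At N = 149 power is 79.8%. So N = 150, as stated.
- Fisher z: ((1.645 + 0.842)/atanh 0.2)² + 3 = (2.487/0.2027)² + 3 = 153.4, i.e. 154, within 3% of 150.

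The figure reproduces. The point concerns the choice of variable and statistic, not the arithmetic.

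**2. When a peak can be known.** With one value per morning, the earliest day on which a maximum can be recognised is peak day + 1, when the first lower value appears. Recognition before the ultrasound day of ovulation (US-DO) requires peak day + 1 < US-DO, so the peak must fall at least 2 days before US-DO. The documents do not give the interval from LH peak to ovulation, so how often this happens cannot be derived from them.

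**3. What rho responds to.** Spearman's rho uses ranks only. For any constant c, rank(peak day + c) = rank(peak day), so rho is the same whether the peak leads or lags ovulation by a fixed amount.

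**4. Illustration.** These inputs are assumptions and not trial figures: ovulation day with SD 3 days, peak-day scatter around its average offset with SD 1 day, days rounded to whole days, recognition one morning after the peak.

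| Average peak position relative to US-DO | Spearman's rho | Cycles with peak recognised before US-DO |
|---|---|---|
| 3 days before | about 0.935 | about 92% |
| 2 days before | about 0.935 | about 68% |
| 1 day before | about 0.935 | about 32% |
| same day | about 0.935 | about 8% |
| 1 day after | about 0.935 | about 1% |
| 3 days after | about 0.935 | 0% |

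One and the same rho fits a marker that nearly always gives warning and one that never does.

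**5. Hypothesis against analysis.**

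| Claim in section 2.1 | Counterpart in the section 3.1 main analysis | Match |
|---|---|---|
| PDG confirms | Day of progesterone elevation against ovulation day | A later marker is what confirmation needs |
| LH predicts | Peak LH against ovulation day | Association only; order and lead time are not measured |

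**The case against.** The strongest reply is that correlation is the stated primary objective. Section 1.4 says so, section 3.1 delivers it, and section 3.3 expects the monitor to identify and confirm ovulation. This stands: the correlation is a proper analysis for that objective. It does not remove the separate claim in section 2.1 and the Abstract that LH predicts.

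Second, sensitivity and specificity are planned, and a positivity rule and window may sit in a full protocol or analysis plan that is not shown. This also stands in part. Such an analysis could test prediction, and the absence of its details from an article is no fault. But the article does not make it the powered main analysis, nor link it to a rule applied as values arrive.

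Third, peak levels is probably loose wording for peak day, given the day-based progesterone half and the day-0 reference. I agree, and the repair is a few words.

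A reader might infer more, and the documents do not bear it out:

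- *That the main analysis cannot support prediction at all.* A strong association is necessary evidence for prediction, though not sufficient.
- *That the peak is known only after the surge has fallen, or often on or after ovulation.* One lower value is enough, and it may still precede US-DO. No lead time is given, and the illustration runs from 0% to about 92%.
- *That a one-day recognition delay is twice the plan's precision target.* The 0.5 days in section 2.4 is a difference the study is said to be able to detect, not a per-user target.
- *That anovulatory cycles inflate the correlation.* They have no US-DO and cannot enter it. LH signals without ovulation are a question of specificity.

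**Conclusion.** The point holds in a limited form. The powered main analysis measures retrospective association between peak LH and US-DO. It does not by itself test whether LH predicts ovulation, because the peak is defined with later values and rho is blind to a constant lead or lag. Both reasons are structural and need no assumed data. The numerical illustration rests on the assumed SDs of 3 days and 1 day and shows only that rho and advance warning can separate completely.

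The size of any overstatement in this trial cannot be given, since it depends on a lead time that the documents do not state. The 150 cycles are not in dispute. The mismatch should be corrected before analysis, but it does not threaten the data collection or the association objective.

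**What to change.** 1. In section 3.1, replace peak levels of LH with day of peak LH, and describe that correlation as evidence of retrospective association.
2. For the prediction hypothesis, define an LH index day: the first day on which a pre-stated LH criterion (a threshold or a rise) is met using only values up to that day. Report its difference in days from US-DO (the lead time), the proportion of cycles flagged before US-DO, and the LH-positive episodes with no ovulation. Tie the LH part of the sensitivity and specificity analysis to the same criterion.
3. Alternatively, keep the analysis and reword the hypothesis in section 2.1 and the Abstract as identification of, or association with, the day of ovulation.

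The cost is wording and a modest amount of extra analysis on daily values already being collected. Apparent accuracy may be lower than for the retrospective peak.
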